#### Primary

Is *Recovery MANTRA* associated with higher BMI at the end of the 6-week intervention relative to treatment as usual alone?

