### Outcome assessment

The primary outcome variable is patient BMI at the end of the 6-week intervention (treatment as usual versus *Recovery* MANTRA). The secondary outcome variables are patient BMI at 6-month and follow-up and eating disorder symptoms (assessed by EDE-Q scores) at 6-week and 6-month follow-up (treatment as usual versus *Recovery* MANTRA). The hypothesized mediators and moderators of primary and secondary outcomes include mood (DASS-21), perceived work or social adjustment (Work and Social Adjustment Scale), motivation and confidence to change (visual analogue scale and ACMTQ), cognitive flexibility, and perceived alliance with therapist and peer mentor. Moreover, the trajectories of change in eating disorder symptoms (weekly EDE-QS), perceived alliance with peer mentors (assessed weekly), and mood, confidence or motivation, connection to others, hope and adherence or satisfaction with treatment plan (assessed daily via ultra-brief surveys) will predict the primary and secondary outcomes. Exploratory outcomes include the impact of guidance delivery on peer mentors’ eating disorder symptoms and mood (assessed via a feedback form) and treatment adherence or fidelity and acceptability (assessed via a feedback form) on secondary outcomes.

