## Expected results

### Quantitative data analysis

This exploratory hypothesis testing study is designed to assess our theorized model of maintenance and change in anorexia nervosa (Figure 1). The time trend in weight and symptoms of anorexia nervosa over 6 months for each person will be estimated using mixed-effects regression models with structured covariance patterns to account for autocorrelation of repeated measures [51,52]. Models will test for linear and curvilinear change over time. The difference between the groups in the rate of change over time will then be examined using group-by-time interaction. Variation within individuals will be modelled as ‘Level 1’ and will include daily survey data, and variation between individuals (including the intercept and slope) will be modelled as ‘Level 2’. All continuous variables will be grand mean centred and results will be modelled using random intercept and slopes. Separate analyses will regress (1) participants’ weight change (baseline to 6-month follow-up) on mood, (2) participants’ weight change (baseline to 6-month follow-up) on motivation to change and on confidence to change and (3) treatment condition on repeated assessment of weight.

Moderator and mediator analyses will be performed using the regression-based bootstrapping approach described by Hayes [53]. Bias corrected bootstrap confidence intervals will be used to test moderators and mediators based upon 10,000 bootstrap samples. Analyses will be conducted using the PROCESS macro [54].

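### The only stated between-group test compares rates of change over 6 months and no week-6 BMI contrast is named, so the plan as written does not test its primary outcome

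*Protocol article*

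**What the plan says.** The primary research question is whether the intervention is "associated with higher BMI at the end of the 6-week intervention relative to treatment as usual alone". The Outcome assessment section agrees: "The primary outcome variable is patient BMI at the end of the 6-week intervention", compared between arms. BMI at 6 months is placed among the secondary outcomes.

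The Quantitative data analysis section is the only text on quantitative analysis of patient outcomes. It says: "The time trend in weight and symptoms of anorexia nervosa over 6 months for each person will be estimated using mixed-effects regression models". On the shape of time it says: "Models will test for linear and curvilinear change over time". On the arms it says: "The difference between the groups in the rate of change over time will then be examined using group-by-time interaction". Three separate regressions follow. The first two use weight change from baseline to 6 months. The third is worded as regressing "treatment condition on repeated assessment of weight" and gives no time point.

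According to Patient assessments, clinicians record weight at baseline and weekly for 6 weeks, and patients report their own BMI once, at 6 months.

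**The concern.** A difference in rate of change over 6 months is not a difference in level at week 6. The two agree only if the arms separate along a straight line for the whole period. Peer support stops at week 6, and the article itself treats week 6 and 6 months as separate questions, so a straight line cannot be taken for granted.

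If the interaction is reported as the treatment result, a benefit at week 6 that later fades could be missed. A difference that appears only after week 6 could be read as success on the primary outcome. The Abstract says the results will inform whether a larger trial is justified, so the error would carry into that decision. With no contrast named, the analyst also has to choose after the fact which coefficient or combination answers the primary question.

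The Sample size section does not fill the gap. It sizes the trial on BMI with a paired-samples t test, which is not a between-arm comparison.

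**Working it through.** The plan gives no figure for this point, so there is none to reproduce. The check asks what the stated test estimates under simple patterns of the arm difference.

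**Inputs**
- Visit times: baseline and weekly to week 6, then 6 months (Patient assessments and Table 1). Taking 6 months as week 26 is an assumption.
- Arm difference D(t): assumed to rise linearly to δ at week 6 and to equal f·δ at 6 months. The article gives neither δ nor f. I use δ = 0.5 kg/m² for illustration.
- Complete data.

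**Leverage of the 6-month point on a linear slope**
- Mean time = (0+1+2+3+4+5+6+26)/8 = 47/8 = 5.875.
- Sxx = Σt² − 8 × 5.875² = 767 − 276.125 = 490.875.
- Share of week 26 = (26 − 5.875)²/490.875 = 405.016/490.875 = 82.5%.

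**Expected linear interaction** = Σ(t − 5.875)·D(t)/Sxx
- Weeks 0 to 6 contribute (δ/6) × (91 − 5.875 × 21) = −5.396δ. Week 26 contributes 20.125fδ.
- Slope = δ(−5.396 + 20.125f)/490.875.
- Fitted week-6 difference = mean of D + slope × (6 − 5.875).

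| Arm difference | True at week 6 | Interaction per week | Fitted at week 6, linear |
|---|---|---|---|
| 0.5 at week 6, gone at 6 months | 0.5 | 0.5 × (−5.396)/490.875 = −0.0055 | 0.219 − 0.001 = 0.22 |
| None through week 6, 0.5 at 6 months | 0 | 0.5 × 20.125/490.875 = +0.0205 | 0.0625 + 0.0026 = 0.07 |
| 0.5 at week 6, fully kept | 0.5 | 0.5 × 14.729/490.875 = +0.0150 | 0.281 + 0.002 = 0.28 |

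**When the interaction reverses sign.** The slope is negative if f < 5.396/20.125 = 26.8%, so less than about 27% of the benefit must persist. I varied three things: 6 months at 26 or 32 weeks, weekly visits or only baseline, week 6 and 6 months, and independent errors or first-order autocorrelation of 0.7 or 0.9 per week. The threshold then runs from 11% to 34%. Stronger autocorrelation weakens the reversal: at 0.95 per week the fading-case slope shrinks to −0.0009. A random intercept and slope with independent residuals gives the same slopes as least squares when data are complete, so that agreement is no evidence of robustness.

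**Quadratic time, same visits (least squares)**
- Fading case: intercept −0.0190, linear +0.1074, quadratic −0.00410. At week 6: −0.0190 + 6 × 0.1074 − 36 × 0.00410 = 0.48, against a true 0.5.
- Late case: 0.005 at week 6, against a true 0.

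The quadratic model contains nearly the right answer, but as a combination of three coefficients. No single interaction coefficient is the week-6 difference.

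**The case against.** The best defence is that the plan does not commit to a straight line. It allows curvilinear change, and the quadratic fit above recovers 0.48 and 0.005, so both damaging patterns largely disappear. Which contrast to read from a fitted model is a detail that an article often leaves to the full protocol or analysis plan. That limits the size of the problem but does not remove it. The article does name a between-group test, that test is the difference in rate of change, and it conflicts with the primary outcome stated elsewhere in the same article.

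A reader might infer that the plan would give the wrong sign for the primary outcome. The documents do not support that. The reversal belongs to the linear interaction coefficient, and only when most of the early benefit is lost. Even in the fading case the linear model's fitted week-6 difference is +0.22: too small, but in the right direction.

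The third regression could be read as covering weeks 0 to 6, because it omits the 6-month span given for the other two. That reading is open, but nothing in the text confirms it. Its reversed wording, which makes the randomised arm the dependent variable, looks like a slip, since the other two are the right way round.

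Finally, the study calls itself exploratory and a feasibility study. It still names one primary outcome and sizes the trial on it.

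**Conclusion.** The point holds in this form: the primary outcome is the between-arm difference in BMI at week 6, the only stated between-group test is a rate of change in a model spanning 6 months, and no week-6 contrast is named. This mismatch does not depend on any assumed trajectory.

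Its numerical effect does. With a linear time term and visits at weeks 0 to 6 and 26, a 0.5 kg/m² benefit that fades gives −0.0055 per week, and a purely late difference gives +0.0205 per week. Even a fully kept benefit of 0.5 is fitted as 0.28 at week 6. These figures rest on the assumed patterns, complete data and week 26, and the sign reversal also needs less than about 27% persistence (11% to 34% across the variants tried up to autocorrelation 0.9). With a quadratic term the numerical harm is small, provided the week-6 contrast is actually requested.

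**What to change.** Name one primary analysis: the baseline-adjusted between-arm difference in BMI at week 6, with its 95% CI, from a repeated-measures model flexible enough to estimate it. Visit as a category with group-by-visit terms would do. So would an explicit week-6 contrast from the curvilinear model already planned. Neither is the only acceptable choice.

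Take the 6-month BMI contrast as secondary, and keep the rate-of-change test as exploratory. Correct the third regression to repeated weight on treatment condition.

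The cost is analysis wording only. The scheduled assessments already provide BMI at every time point needed.

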*Recovery* MANTRA integrates two novel strategies to provide peer support to individuals with anorexia nervosa. The first strategy involves offering a library of recorded personal recovery narratives (derived from interviews with formerly ill individuals) that describe successful change steps and the nonlinear process of recovery. A feasibility and acceptability study of an early prototype of the guided self-help intervention in a community sample of participants with anorexia nervosa was promising; participants exhibited weight increases and symptom improvement subsequent to the intervention [32]. Previous test trials have demonstrated that watching similar video podcasts (‘vodcasts’) to support eating or improve positive mood lead to increases in test meal consumption and reductions in anxiety and negative thoughts [33,34]. Feedback from participants, carers, and professionals has led to improvements in these materials [18].

The second strategy to provide peer support in *Recovery* MANTRA involves weekly text-based guidance from peer mentors with personal experience of eating disorders. These online guidance sessions are designed to enhance motivation and complement the participant’s use of a self-care workbook. Preliminary evidence regarding the use of peer mentors for psychological interventions is encouraging. For instance, a Cochrane systematic review examining evidence of the effectiveness of consumer providers of care concluded that these providers were as effective as statutory mental health services [35]. Moreover, the use of peer mentors as support for people with eating disorders has been found to improve these people’s quality of life and increase adherence with services [36]. However, the quality of the guidance has been found to be an important factor in shared information approaches [5] and thus rigorous, standardized training and supervision of peer mentors is an integral component of delivering an efficacious intervention. Indeed, research suggests that training of nonspecialized professionals is an important factor in enhancing feasibility of task-sharing interventions [37]. We have previously had success in training people with experience of eating disorders (mainly as caregivers) to provide a form of motivational interview-based support to other families [38] and will therefore follow the same strategy for training peer mentors in *Recovery* MANTRA.

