### Sample size

Previous research suggests that the effect size for increases in BMI subsequent to a guided self-help intervention is 0.29 [6]. To detect the same level of change in our primary outcome variable (BMI) using a paired-samples *t* test (*α* = 0.05, *β* = 0.20), a minimum of 90 participants would be required per study arm. However, owing to limited resources and because this is a feasibility study, we expect to recruit 75 participants per arm (resulting in total *N* = 150). This would enable us to detect an effect size of 0.33 or larger (*α* = 0.05, *β* = 0.20).

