#### Guided self-help (Recovery MANTRA)

Participants allocated to the *Recovery* MANTRA condition will receive self-help materials and weekly guidance from a peer mentor to supplement their treatment as usual. The self-help materials include a collection of short video clips (‘vodcasts’) that describe various strategies for behaviour change, anxiety management techniques, and recovery narratives generated by individuals with personal experience of eating disorders. The vodcasts are accompanied by (and signposted in) a self-care workbook. The workbook provides supplemental information and offers the rationale for the behaviour change steps proposed. The intervention materials were developed with the aim of increasing confidence to change, internalized motivation, connectedness to others and hope. In addition, the participants will be offered individualized support via online text chat (using a secure platform) through peer mentors for a maximum of one hour each week over 6 weeks. The peer mentor will contact the participants to introduce the materials and to provide information about the parameters of support (see Table 2 for programme of guidance).

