In total, 10 to 15 peer mentors will be trained, to allow for attrition. The purpose of the guidance is not to provide an additional stand-alone intervention, but rather, to offer support to patients in using the self-help materials effectively and purposefully. Peer mentors are individuals with past experience of eating disorders who have sufficient time for training, supervision and coaching and are trained in professions allied to medicine or equivalent (psychology, counselling) or teaching. Individuals with clinically significant levels of baseline anxiety, depression or eating disorder symptoms are excluded. Comprehensive training for task-sharing interventions involves three important components: participation in an introductory workshop delivered by an expert, reading or review of workbooks or other written materials that detail the intervention, and administration of the intervention under close supervision of treatment experts [2]. Peer mentors will receive all of these training components prior to delivering the *Recovery* MANTRA intervention.

The curriculum currently used for training and supervision of carer coaches will be adapted for training peer mentors. In particular, the peer mentors will receive three days of training in motivational interviewing, during which they will also become familiarized with the *Recovery* MANTRA materials and practise using the online text-chat delivery system. For the duration of their involvement in the project, the peer mentors will also receive weekly clinical supervision and will undergo regular assessment of their eating disorder symptoms and mood. Copies of the text-chat messages between the peer mentor and the participant will be used for supervision and to assess treatment quality and fidelity.

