### Fidelity and adherence to model

Peer mentors will be assigned study participants only after they have demonstrated sufficient competence with training samples (that is, the training samples will have details of patients who will not be used within the study). Adherence and fidelity to the motivational interviewing model will be monitored by an analysis of a random selection of transcripts (sessions 2 to 5) using the Motivational Interviewing Treatment Integrity rating system, a validated and reliable behavioural coding system used to measure treatment integrity in motivational interviewing [38]. A simplified version of the Revised Cognitive Therapy Scale [39] will be adapted specifically for this intervention to address the more goal-driven aspects of the programme.

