#### Qualitative studies A and B

Participants (*n* = 75) and peer mentors (*n* = 10 to 15) will be asked to complete a feedback form at the end of the intervention. Questions will focus on overall experience of participation, use and acceptability of materials, relationship with peer mentor or participant, any particular learning points, challenges met, and suggestions for improvement. A thematic analysis will be used to analyze data from the written feedback forms [55].

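### The two-level model stops at the participant, although about 75 intervention participants share 10 to 15 peer mentors; if outcomes correlate within mentor, the treatment standard error is understated

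*Protocol article*

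**What the plan says.** In the protocol article, the Guided self-help (Recovery MANTRA) section says that intervention participants "will receive self-help materials and weekly guidance from a peer mentor to supplement their treatment as usual". The treatment-as-usual arm has no mentor. The same section states: "In total, 10 to 15 peer mentors will be trained, to allow for attrition". The Sample size section says "we expect to recruit 75 participants per arm". Mentors take on several participants each, after a competence check: "Peer mentors will be assigned study participants only after they have demonstrated sufficient competence" (Fidelity and adherence to model).

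The Quantitative data analysis section names the levels of the model: "Variation within individuals will be modelled as" Level 1, and "variation between individuals (including the intercept and slope) will be modelled as" Level 2, with random intercepts and slopes. The groups are compared through the group-by-time interaction. Neither this section nor the Sample size section mentions a mentor level, a cluster-robust variance or a mentor ICC. The one intraclass correlation in the article, under Subsidiary analysis of peer mentors, concerns agreement between raters of mentor competence.

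**The concern.** Participants guided by the same mentor share that mentor's skill, style and persistence, so their outcomes may be more alike than those of participants with different mentors. This can happen only in the intervention arm, which makes the design partially nested. A model that stops at the participant treats all 150 as independent apart from what it names.

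The article itself gives reason to take this seriously. The Background says that "the quality of the guidance has been found to be an important factor in shared information approaches". The Outcome assessment section lists alliance with the mentor among the hypothesised mediators and moderators, and its weekly course as a predictor of outcome. A plan that expects the mentor relationship to affect outcome has little ground for fixing mentor variance at zero.

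At stake is the width of the treatment confidence interval, and so the evidence on which the Abstract says a larger trial will be judged justifiable and feasible.

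**Working it through.** **The plan's own figure.** The Sample size section gives a detectable effect of 0.33 with 75 per arm (paired t test, alpha 0.05, power 0.80). Assuming a two-sided test, the noncentral t calculation gives 0.328, so the figure reproduces. It contains no allowance for mentors. Whether a paired test suits a between-group question is a separate matter, not pursued here.

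**Inputs.** From the article: n = 75 per arm and k = 10 to 15 mentors trained. Assumed: equal load per mentor, and an ICC of 0.01 to 0.10. A case of k = 8 active mentors is added because the article expects attrition.

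**Formulas.**
- Participants per mentor: m = 75/k, giving 75/15 = 5 and 75/10 = 7.5.
- Design effect in the intervention arm: DE = 1 + (m − 1) × ICC.
- True SE divided by reported SE, with clustering in one of two equal arms: √((1 + DE)/2).
- Actual coverage of a nominal 95% interval: 2Φ(1.96/ratio) − 1.

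Example with k = 10 and ICC 0.05: DE = 1 + 6.5 × 0.05 = 1.325; ratio = √(2.325/2) = 1.078.

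| Mentors (m) | ICC | DE | SE ratio | Coverage |
|---|---|---|---|---|
| 15 (5) | 0.01 | 1.040 | 1.010 | 94.77% |
| 15 (5) | 0.02 | 1.080 | 1.020 | 94.54% |
| 15 (5) | 0.05 | 1.200 | 1.049 | 93.83% |
| 15 (5) | 0.10 | 1.400 | 1.095 | 92.64% |
| 10 (7.5) | 0.01 | 1.065 | 1.016 | 94.63% |
| 10 (7.5) | 0.02 | 1.130 | 1.032 | 94.25% |
| 10 (7.5) | 0.05 | 1.325 | 1.078 | 93.09% |
| 10 (7.5) | 0.10 | 1.650 | 1.151 | 91.14% |
| 8 (9.4) | 0.05 | 1.419 | 1.100 | 92.53% |

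The effective intervention-arm size, 75/DE, falls to 62.5 or 56.6 at ICC 0.05 and to 53.6 or 45.5 at ICC 0.10 (15 or 10 mentors).

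**Simulation.** Two sets of runs (20,000 and 40,000 per setting) applied an ordinary two-sample t test to data clustered in one arm. With 15 mentors, type I error was 6.4-6.6% at ICC 0.05 and 7.3% at 0.10. With 10 mentors it was 7.0-7.2% and 9.0-9.1%. At ICC 0.01-0.02 it was 5.2-5.8%, and at zero 4.9-5.2%.

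**Link to the planned test.** These calculations concern one measurement per person. With complete data on a common schedule, the group-by-time estimate compares mean individual slopes, so the same formulas apply with the ICC of the slopes. A smaller simulation of the longitudinal model (10 mentors, 75 per arm, seven weekly time points, assumed slope ICC 0.10, 400 REML fits) gave:
- Empirical SE of the interaction: 0.154.
- Model SE without a mentor term: 0.135 (0.154/0.135 = 1.14, in line with the table).
- Model SE with a mentor random intercept: still 0.135, type I error 7.75%.
- Model SE with a mentor random slope: 0.150, type I error 6.25%, with the mentor variance estimated at about zero in 27% of fits.

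With 400 fits the Monte Carlo error on 7.75% is √(0.0775 × 0.9225/400) ≈ 1.3 percentage points. The two error rates cannot be told apart reliably, but the contrast in standard errors is clear.

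**The case against.** The best argument on the other side is that mentor variance may be very small. All participants use the same workbook and vodcasts. Guidance is text chat for no more than an hour a week over six weeks. Mentors are trained, supervised weekly and checked for fidelity, and both arms receive usual treatment, which also drives BMI. This favours the low end of the ICC range, where the effect is negligible. It stands as a reason to expect a small ICC, but these measures reduce mentor differences without modelling them. Centre stratification does not help either: there are more than 25 services and at most 15 mentors, so centre cannot stand in for mentor.

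A second argument is that a condensed article need not list every model term. It promises, for example, to take centre differences in usual treatment into account, yet the analysis section names no centre term. That is fair, and the full analysis plan may add a mentor term. But the article is not silent on the random structure: it names the levels and ends at the individual, and makes no similar promise for mentors.

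Third, the trial is described as exploratory and as a feasibility study, so an error of 5-8% in the SE would rarely change the decision to proceed. That limits the severity, but it does not remove the need to learn the mentor variance before a larger trial.

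A reader might also infer that the plan overlooks mentor differences altogether. It does not: the exploratory research questions ask whether mentors work consistently and whether fidelity predicts six-month outcome. What is missing is their place in the treatment comparison.

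**Conclusion.** The omission is plain from the text: mentors exist in one arm only, and the stated model has no level for them. The harm is conditional. A reader might conclude that the interval is certainly too narrow and that type I error certainly exceeds 5%. The documents do not support that, because they give no mentor ICC, and with an ICC of zero nothing is lost.

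Over the assumed range the true SE exceeds the reported one by about 1-3% at ICC 0.01-0.02, 5-8% at 0.05 and 10-15% at 0.10. Type I error is about 6.4-7.2% at 0.05 and 7.3-9.1% at 0.10. These figures assume 10 to 15 active mentors with equal loads. Fewer mentors make the effect larger (10% on the SE with 8 mentors at ICC 0.05), and so would unequal loads.

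This is a modest, possibly negligible, effect with an inexpensive remedy, and worth correcting before analysis.

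**What to change.** Record the mentor ID for every intervention participant. Chat transcripts are already kept for supervision and fidelity, so the link probably exists.

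Use a partially nested model with mentor-level variation in the intervention arm only and each control as a singleton. Where treatment is tested by group-by-time, include a mentor random slope, because a mentor intercept alone leaves that standard error essentially unchanged. Where BMI or EDE-Q is compared at a single time point, a mentor random effect on that outcome is enough. Use Satterthwaite or Kenward-Roger degrees of freedom, and state in advance what is done if the mentor variance is estimated as zero. Report the mentor variance or ICC with its confidence interval for planning the larger trial.

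The cost is a small change to the model and a slightly wider interval. With 10 to 15 mentors the variance will be imprecise and zero in some fits, so the reported ICC should be read as a range and not as a firm planning value.

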### Randomization

Participants will be randomized by an independent researcher using stratified randomization by centre and illness severity (severe illness will be defined as BMI <16 kg/m^2^). Once the database has returned a participant’s group allocation, no changes can be made.

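### The third of the separate regressions has its terms transposed: as written it models randomised allocation from weight and gives no between-arm BMI difference (minor)

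*Protocol article*

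**What the plan says.** Under Expected results, Quantitative data analysis, the protocol article first describes a longitudinal model: "The time trend in weight and symptoms of anorexia nervosa over 6 months for each person will be estimated using mixed-effects regression models". It then gives the treatment comparison within that model: "The difference between the groups in the rate of change over time will then be examined using group-by-time interaction".

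The same paragraph ends with three further regressions, governed by a single verb:

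- Item 1: "Separate analyses will regress (1) participants’ weight change (baseline to 6-month follow-up) on mood".
- Item 2: "weight change (baseline to 6-month follow-up) on motivation to change and on confidence to change".
- Item 3: "3) treatment condition on repeated assessment of weight".

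The primary research question is whether the intervention is "associated with higher BMI at the end of the 6-week intervention relative to treatment as usual alone". The Randomization section fixes allocation permanently: "Once the database has returned a participant’s group allocation, no changes can be made".

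**The concern.** To regress A on B means that A is the dependent variable and B the predictor. Items 1 and 2 follow that order: weight change is explained by mood, then by motivation and confidence. Item 3 falls under the same verb, so its dependent variable is treatment condition and its predictor is weight. The trial asks the opposite, namely whether allocation changes BMI.

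Item 3 is the only one of the three listed regressions that contains treatment. An analyst who followed it to the letter would obtain a coefficient describing how weight readings, possibly including those taken before treatment began, relate to the arm a person was assigned to. That coefficient is not in BMI units and does not estimate the effect of the intervention. The paragraph would also hold two analyses of treatment and weight that run in opposite directions.

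**Working it through.** The plan gives no figure for this item, so there is none to reproduce. The check has four steps.

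**1. Direction of each stated analysis**

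| Analysis in the paragraph | Dependent variable | Predictor |
|---|---|---|
| Mixed model with group-by-time term | weight (and symptoms) over time | group, time, group × time |
| Item 1 | weight change | mood |
| Item 2 | weight change | motivation; confidence |
| Item 3, as written | treatment condition | repeated weight |

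Only item 3 does not have weight or symptoms as the outcome.

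**2. What the reversed coefficient estimates**

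Let T be allocation (0 or 1), W weight or BMI at one visit, r their correlation, and s_T and s_W their standard deviations.

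- Correct direction: slope = r × s_W / s_T. For a binary T this is the difference in mean W between the arms.
- Reversed: slope = r × s_T / s_W. This is a change in the probability of belonging to one arm per unit of W.
- In both directions: t = r × √[(N − 2) / (1 − r²)]. With the planned N = 150 there are 148 degrees of freedom.

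The test of no association at a single visit is therefore identical either way. What is lost is the estimate. A simulation with 75 per arm and 1,000 data sets per scenario (variances and effect assumed) agrees. The largest difference between the two p-values was about 3 × 10⁻¹⁵. Rejection was 0.78 in both directions under the assumed effect and 0.061 in both under no effect.

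**3. Repeated weights with a random participant intercept**

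Taken literally in the random-intercept framework of the same paragraph, item 3 becomes

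T_i = a + b × W_ij + u_i + e_ij,

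where i is the participant and j the visit. The left side is the same at every visit. Setting b = 0 and u_i = T_i − a fits every row exactly with e_ij = 0. Any other b leaves residuals that vary with within-person changes in weight. The residual variance is driven to zero and b is forced to zero whatever the treatment does. The model is degenerate.

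**4. Does the reversal itself alter error rates?**

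The design was simulated changing direction only. The inputs were 75 per arm (Sample size section) and 8 readings: baseline, weeks 1 to 6 and month 6 (Table 1). The remaining inputs are assumptions: residual SD 0.3 kg/m², between-person SD 0.8 or 1.5 kg/m², random slope SD 0.05 per week, a true week-6 difference of 0 or 0.4 kg/m², no dropout, 400 replicates. Paired values are for between-person SD 0.8 and 1.5.

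| Analysis | True difference | Weight on arm | Arm on weight |
|---|---|---|---|
| All rows pooled, clustering ignored | 0 | 48%, 51% | 48%, 51% |
| All rows, participant-robust errors | 0.4 | 37%, 16% | 35%, 15% |
| Week 6, baseline-adjusted | 0.4 | 99.8%, 99.5% | 99.8%, 99.5% |

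Within each row the two directions agree to within about 2 points. The differences between rows come from whether clustering is respected and whether baseline is adjusted for.

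**The case against.** The strongest reply is that this is a slip of word order whose meaning is clear from context. The primary question and the Outcome assessment section both treat BMI as the outcome compared between arms. The group-by-time sentence just before the list has weight as outcome and group as predictor. A singular random-intercept fit would be noticed and corrected rather than reported as a null trial. Most of this stands, and it is why the point is minor.

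A reader might infer two stronger things.

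- **That the plan cannot test whether the intervention changes weight.** The documents do not support this. The group-by-time interaction is a correctly directed test, and even the reversed regression at a single visit tests the same null hypothesis.
- **That the reversal costs power or inflates false positives.** A reversed, pooled analysis does reject about half the time under no effect, and a reversed analysis without baseline adjustment has far less power than a baseline-adjusted week-6 comparison. The same rates appear in the correct direction, so the reversal is not the cause. Pooling rows as if independent would also contradict the paragraph's own provision for correlation between repeated measures.

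The context does not make the sentence right, however. Item 3 is announced as a separate analysis. The group-by-time test concerns rate of change in a model of the 6-month trend and does not directly give the between-arm BMI contrast at week 6, which is the primary outcome.

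**Conclusion.** Item 3 is wrong as written and is most plausibly a transposition. Read in the order set by items 1 and 2, it makes an allocation that is fixed by randomisation the dependent variable. It gives no between-arm difference in BMI, and it is degenerate when fitted with a random participant intercept. These conclusions follow from the wording and from the algebra, not from any assumed variance.

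The consequence is confined to this one item. No sample size, power or type I error figure in the plan changes because of it. The finding that error rates do not depend on direction is exact for linear regression at a single visit. For the pooled repeated-weight models it rests on simulation under the stated assumptions. Severity: minor.

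**What to change.** Restate item 3 as a regression of repeated BMI on treatment condition, with participant as the clustering unit and baseline BMI as a covariate. Report the adjusted between-arm BMI difference at 6 weeks (primary) and at 6 months (secondary).

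Swapping the terms is enough to repair the error. The baseline covariate and the named time points go a little further: they make the item deliver the week-6 contrast that the primary question asks for, alongside the existing group-by-time test.

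The cost is one sentence in the analysis section. Baseline, weekly, end-of-intervention and 6-month BMI are already in the assessment schedule (Table 1), so no new data, patients or visits are needed. If the correct direction was always intended, little more than the wording changes.
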